## Abstract

**Background:**

The World Health Organisation suggests that simplification of the medical abortion regime will contribute to an increased acceptability of medical abortion, among women as well as providers. It is expected that a home-based follow-up after a medical abortion will increase the willingness to opt for medical abortion as well as decrease the workload and service costs in the clinic.

**Methods/Design:**

This study protocol describes a study that is a randomised, controlled, non-superiority trial. Women screened to participate in the study are those with unwanted pregnancies and gestational ages equal to or less than nine weeks. The randomisation list will be generated using a computerized random number generator and opaque sealed envelopes with group allocation will be prepared. Randomization of the study participants will occur after the first clinical encounter with the doctor. Eligible women randomised to the home-based assessment group will use a low-sensitivity pregnancy test and a pictorial instruction sheet at home, while the women in the clinic follow-up group will return to the clinic for routine follow-up carried out by a doctor. The primary objective of the study this study protocol describes is to evaluate the efficacy of home-based assessment using a low-sensitivity pregnancy test and a pictorial instruction sheet 10–14 days after an early medical abortion. Providers or research assistants will not be blinded during outcome assessment. To ensure feasibility of the self-assessment intervention an adaption phase took place at the selected study sites before study initiation. This resulted in an optimized, tailor-made intervention and in the development of the pictorial instruction sheet with a guide on how to use the low-sensitivity pregnancy test and the danger signs after a medical abortion.

**Discussion:**

In this paper, we will describe the study protocol for a randomised control trial investigating the efficacy of simplified follow-up in terms of home-based assessment, 10–14 days after a medical abortion. Moreover, a description of the adaptation phase is included for a better understanding of the implementation of the intervention in a setting where literacy is low and the road-connections are poor.

**Trial registration:**

Clinicaltrials.gov NCT01827995. Registered 04 May 2013.

## Background

The maternal mortality ratio in India decreased from 570 in 1990 to 178 per 100,000 live births in 2010
[1,2]. Despite these remarkable gains, India remains responsible for 20% of maternal deaths globally
[3]. Abortion represents 8-18% of maternal deaths in India today even though abortion is legal since the Medical Termination of Pregnancy (MTP) Act went into effect in April 1972
[4,5]. Unsafe abortion is defined by the World Health Organization (WHO) as a procedure for terminating an unintended pregnancy carried out either by persons lacking the necessary skills or in an environment that does not conform to minimal medical standards, or both
[6].

According to the MTP Act, abortions are legal up to 20 weeks if the mother’s life is at risk, if the foetus suffers from severe abnormalities or, if the contraceptive method used, fails to prevent pregnancy. Governmental facilities may provide abortion care if employing a practitioner trained to provide abortions. Private clinics, on the other hand, need a governmental approval to be allowed to conduct abortions
[7]. In spite of the existing legal framework in India, a literature review from 2002 suggests that only 15% of abortions are performed within this legal framework
[8]. Apart from lack of access, this may be explained by women’s lack of awareness of the legal status of abortions and thus they opt for illegal providers. Concerns about confidentiality, cost and quality of available services are other reasons reported to affect women’s choice of abortion provider
[9]. In 2002, the Drug Controller of India approved the use of mifepristone for the purpose of termination of pregnancy up to 49 days of gestation. In 2006, misoprostol was approved for treating gynaecological conditions, including early abortions
[10]. In 2008, the Central drug standard control organisation approved the combipack (1 tablet of mifepristone 200 mg and 4 tablets of misoprostol 200 mcg) for medical abortion for up to 63 days of gestation, although the MTP Act still state 49 days as the limit for medical abortion
[11]. Medical abortion is feasible and acceptable in India
[12,13], however, implementation of medical abortion as an alternative to surgical abortion has been slow on a national scale. As of 2008 only 3% of qualified abortion providers reported to provide medical abortion, and 23% intended to do so in the future
[14].

Medical abortion using a combination of mifepristone and the prostaglandin E1 analogue misoprostol is globally recognized as a safe and effective method for induced abortion
[15,16]. Women’s acceptability of medical abortion is influenced by factors such as duration and amount of bleeding, experienced pain during the procedure and the number of clinical visits required
[17]. Moreover women seem to prefer a medical, non invasive, method rather than a surgical method
[18]. The standard procedure for medical abortion in India commonly requires three clinical visits carried out by a physician
[11]. Existing WHO guidelines suggest that a medical follow-up is not necessary after an uncomplicated medical abortion. This is applicable for women with a gestational age up to 12 weeks, if the woman receives proper counselling at the time of her abortion. Although a clinical visit may not be required, follow-up is important to detect an on-going pregnancy
[19]. The current practise of three clinical visits results in considerable service costs and misuse of resources. A number of studies establish the feasibility and safety of home-administration of misoprostol
[20-23]. Recent studies, majority of which are survey studies with small study samples, evaluate alternative means of follow-up after a medical abortion
[24-26]. Another study demonstrates that follow-up can be carried out using remote communication technologies
[27]. Moreover, women conducting a low-sensitivity urinary pregnancy (LSUP) test two weeks post early medical abortion in combination with a telephone follow-up by a health provider has been implemented as standard procedure in a general hospital in Edinburgh
[24,28]. Other studies proved feasibility of self-assessment with a high sensitivity pregnancy test at 30 days after abortion or a semi-quantitative pregnancy test post abortion, both combined with a telephone follow-up
[25,26,29]. The above mentioned studies required the informants to own a phone, be literate, have access to proper infrastructure such as road connections and the presence of readily accessible emergency care and majority were carried out in high-income countries
[25,26,30]. The absence of these conditions would raise a question of feasibility of simplified follow-up in a low-resource setting. The WHO request more evidence regarding self-assessment in their technical guideline for safe abortions
[19].

## Methods/Design

### Aim and hypothesis

This randomised controlled trial (RCT) aims to evaluate the efficacy of home-based assessment after an early medical abortion as well as the acceptability and feasibility of the intervention in a low-resource setting. We hypothesize that home-based assessment after early medical abortion will be as effective as routine clinic follow-up and will increase women’s acceptance towards medical abortion. This study protocol describes the design and method of the RCT along with the course of adaptation and implementation of the study intervention.

### Participating institutions

The Department of Women’s and Children’s Health at Karolinska Institutet in Sweden; the Division of Reproductive Health at Action Research and Training for Health (ARTH) Society, Udaipur in India and the Department of Women’s and Children’s Health at Uppsala University in Sweden designed and developed the study collaboratively. The study follows CONSORT guidelines and is registered at Clinicaltrials.gov (No. NCT01827995).

### Ethical approval

The Institutional Ethics Committee of ARTH has given ethical approval of the study and the Indian Council of Medical Research has approved the participating institutions to carry out the study in India.

### Definitions

In this study, we define complete abortion as when no signs of pregnancy or retention of product of conception (POC) is present, or upon a negative LSUP test, and no further treatment is needed for termination of the pregnancy. We define incomplete abortion as partially retained POC, sometimes with an enlarged size of the uterus or a positive LSUP test. Incomplete abortion requires further treatment, preferably with additional misoprostol or manual vacuum aspiration (MVA). We define on-going pregnancy as persistent pregnancy symptoms, no POC expulsion and enlargement of the uterus
[19]. Moreover, with the LSUP-test we are referring to the combined low- and high- sensitivity pregnancy test purchased from VEDA.LAB (http://www.vedalab.com). The high-sensitivity component is equal to a standard pregnancy test and has a sensitivity of 5 units/litre. The low-sensitivity component has a sensitivity of 1000 units/litre, and is suitable for the use to assess abortion outcome at 10–14 days post abortion. In this study, the low-sensitivity component is of interest, however since there are no separate LSUP tests available on the market we used the combined test. Moreover, the test used in this study is not available in India, however several international pregnancy test manufacturers are currently working to develop LSUP-tests, and its availability on the market is likely to increase in the near future.

### Study setting

ARTH, a not for profit public health organisation, operates three rural and one urban clinic in and around Udaipur in the southern part of Rajasthan state in India. ARTH’s three rural clinics cater to women living in an area characterized by poor road connections, poverty, and low literacy among women (48.5%). The women in this area belong to different social groups, where about half the population belong to the marginalized groups, scheduled caste or scheduled tribe. Apart from carrying out domestic work, women in this area are largely engaged in marginal farming, wage labour and animal husbandry. In contrast to the rural clinics, ARTH’s urban clinic caters to a wider range of women, however majority from a low socioeconomic stratum. The services were made available at the ARTH clinics at a cost to the use of about 4 USD equivalent. To increase the urban sample, we approached two private nursing homes known to provide medical abortion in the city of Udaipur to act as study sites. Their services, subsidized for the purpose of the study, range between 6.5 and 16 USD. In total six clinics, three urban and three rural clinics were included as study sites. Approximately 550 women receive MTP from ARTH’s health centres annually, and of these about 450 women opt for medical abortion. The summarized caseload of the private clinics is an estimated 100 medical abortions per year. Home administration of misoprostol accounts for about 40% of all medical abortions.

Inclusion criteria:

–Women with unwanted pregnancies, who opt for medical abortion at any of the six above described study sites.

–Gestational age of less than or equal to nine weeks, as assessed by an obstetrician.

–Residing within the identified study area consisting of 70 villages in a range of 25 km from the rural clinics (at the rural clinics only).

–Agree to follow-up after 12–15 days, by either phone or home-visit.

Exclusion criteria:

–Women with known contraindications to medical abortion, as assessed by the doctor

–Haemoglobin-value less than 8.5 g/l.

–Younger than 18 years

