### Sample size

The success rate of medical abortion is 95%
[31,32] resulting in a complication rate estimation of 5% in both groups. The primary outcome define the sample size estimation where the 5% non-inferiority margin (delta) establishes the non-inferiority of the home-based self-assessment following medical abortion as compared to the routine clinic follow-up. The delta margin is defined by the clinical assessment standpoint where a 5% difference does not have clinical importance. To proof the non-inferiority of the intervention at a significance level of α = 0,05 and a power of 80%, 596 women are needed. The lost to follow-up estimation of 20%, based on field-testing in the study area, resulted in a final sample size of 716 women. A two-sided 95% confidence interval (CI) (or a one-sided 97,5% CI) will determine the difference in percentage of women requiring surgical intervention from the two groups.

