### Measures

#### Socio-demographic and reproductive background data

Measures such as age, marital status, education level, caste and residential area will compile the socio-demographic information about the study participants. Moreover, the personal reproductive history will be recorded as number of births, number of living children, previous abortions, caesarean section and contraceptive use. Haemoglobin and the gestation will also be measured and recorded.

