## Discussion

This paper summarizes the implementation and administration of an RCT that seek to test the feasibility and efficacy of home-based assessment after an early medical abortion using an LSUP-test and a pictorial instruction sheet. The intervention is designed to accommodate disadvantaged women living in remote as well as urban areas of India. This paper describes the study protocol of an RCT along with the course of adaptation and implementation of the study-intervention.

To increase generalizability of the results, exclusion criteria are limited to those of clinical importance to maintain the safety of the women. Due to the study design, women attending the rural clinics that are residing outside the defined study area will be considered ineligible. However, the study area includes 70 villages, where each village hosts approximately 10.000 inhabitants, including women from different socio-economic strata and with different educational backgrounds. Moreover, no area restrictions are applied to the women recruited in the urban clinics. Thus the sample will be generalizable. The sample size calculation is based on the likelihood of an early medical abortion resulting in a complete abortion (95%), rather than the likelihood of an on-going pregnancy (1-2%). This may limit the ability to identify the clinically important finding of on-going pregnancy. However, it is the commonly used outcome for trials investigating efficacy and safety of medical abortion due to its high success rate. This has been done similarly in trials by the WHO and Sunde-Oppegard et al. investigating schemes of follow-up after medical abortion
[35]. With the additional assumption of a loss to follow-up of 20% based on the field testing, the total study sample required is 716 women, where 298 women with evaluated end point in each group is required to maintain power.

All recruited RAs have been working in the field under ARTH for several years, in their designated field area. This is considered a benefit, as it will diminish suspicion from neighbours during home visits, ensuring confidentiality of the women in the study.

Wolff argues that to conduct a service effectiveness study it is crucial that the intervention is accurately implemented and consistently operationalized throughout the study
[38]. In addition, this needs to be recorded and described in detail so that it can be replicated elsewhere

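### The haemoglobin exclusion is printed as below 8.5 g/l (0.85 g/dl), so read literally it excludes effectively nobody; value and unit need to be reconciled

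*Protocol article*

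**What the plan says.** The protocol article, Study setting, lists three exclusion criteria. One is an age limit. One is left to clinical judgement: "Women with known contraindications to medical abortion, as assessed by the doctor". The third is the only one with a laboratory limit: "Haemoglobin-value less than 8.5 g/l".

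Haemoglobin appears in one other place, under Socio-demographic and reproductive background data: "Haemoglobin and the gestation will also be measured and recorded". That sentence gives neither a unit nor a threshold. No section defines anaemia or gives a second haemoglobin figure.

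The Discussion states what the exclusions are for: "exclusion criteria are limited to those of clinical importance to maintain the safety of the women". The haemoglobin criterion is therefore meant to keep some women out.

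**The concern.** The printed limit lies far below any haemoglobin that a woman walking into a clinic could plausibly have. A criterion that nobody can meet does no work, which conflicts with the purpose the Discussion gives it.

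Two things are at stake. The first is the safety screen. Bleeding is among the side effects to be evaluated (Secondary study outcome), and the follow-up interview asks about heavy bleeding (Follow up of home-based assessment group on day 12–15), so a haemoglobin limit has an evident purpose in this trial. The second is the description of the study population. The Discussion argues that an intervention must be described closely enough to be repeated elsewhere, and a reader cannot tell from the printed criterion which women were ineligible on haemoglobin.

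**Working it through.** **Inputs from the protocol article**
- Threshold and unit: below 8.5 g/l (Study setting).
- Planned total: the loss-to-follow-up allowance "resulted in a final sample size of 716 women" (Sample size). It is used here only as a scale. It counts women to be enrolled, and the number to be screened is not given.

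**Input that is an assumption**
- The documents give no haemoglobin distribution. I take it as normal, with a mean of 80 to 120 g/l and a standard deviation (SD) of 10 to 20 g/l. The lower means are deliberately pessimistic.

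**Step 1: unit conversion.** 1 g/dl = 10 g/l. So 8.5 g/l ÷ 10 = 0.85 g/dl. The same digits read per decilitre would be 8.5 × 10 = 85 g/l. The two readings differ by 85 ÷ 8.5 = 10.

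**Step 2: how many women fall below the printed limit.** P(Hb < 8.5 g/l) = Φ((8.5 − mean) ÷ SD), and the expected count is 716 × P.
- Worst case, mean 80 and SD 20: z = (8.5 − 80) ÷ 20 = −3.575, P = 0.000175, count = 716 × 0.000175 = 0.125.
- Mean 100 and SD 20: z = −4.575, P = 0.0000024, count = 0.0017.

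| Assumed mean (g/l) | SD 10 | SD 15 | SD 20 |
|---|---|---|---|
| 80 | < 0.00001 | 0.00067 | 0.125 |
| 90 | < 0.00001 | 0.00002 | 0.016 |
| 100 | < 0.00001 | < 0.00001 | 0.0017 |
| 110 | < 0.00001 | < 0.00001 | 0.00014 |
| 120 | < 0.00001 | < 0.00001 | < 0.00001 |

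Entries are expected women below 8.5 g/l per 716. Even in the worst case, about 1 ÷ 0.000175 ≈ 5,700 women would have to be screened to expect one exclusion. The normal tail is itself generous this far out.

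**Step 3: how many women's eligibility turns on the unit.** Over the same grid, the share below 85 g/l runs from 0.02% (mean 120, SD 10) to 69% (mean 80, SD 10). That range is too wide to use. The documents do not allow the affected share to be estimated, and this step does not imply that 85 g/l is the right limit.

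**Step 4: does another section repair it?** The only other mention of haemoglobin carries no unit or limit, so it does not.

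No sample size, power or significance figure depends on the criterion, so the plan has no design figure to reproduce here.

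**The case against.** The strongest reply is that nobody would apply the limit as printed. Under All women - recruitment of women on day 1, a doctor first judges eligibility for medical abortion, and the clinical eligibility for the study is then assessed. The research assistant handles only the non-clinical criteria. Staff are trained, each site has a manual, and both follow-up procedures were field-tested, on 33 and 36 women. A clinician would see at once that 0.85 g/dl is absurd. The article also condenses a protocol that is not shown, so the slip may exist only in print. All of this stands, and it limits the practical consequence. It does not make the printed criterion right.

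Four stronger readings are tempting, and the documents do not carry them.
- **Severely anaemic women were enrolled.** Nothing shows this. The doctor-assessed contraindication criterion may catch some of them. The contraindications are not listed, so that backstop is possible but unproven.
- **A database check in the printed unit would never flag anyone.** Data management describes a tested query program for logical and range errors but does not say how haemoglobin is coded. If values are entered in g/dl and compared with 8.5, the check works whatever label is printed. It fails only if values are entered in g/l against that number.
- **The home-based group is left without a safety net.** A research assistant contacts these women on day 12–15, asks about heavy bleeding and weakness, and may refer them. This is not a clinical examination, but it is not nothing. Eligibility is settled before randomisation, so the slip cannot bias allocation.
- **Only the unit is wrong and the number is right.** That is the likeliest explanation, but the document does not establish it.

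**Conclusion.** The point holds for the criterion as written. A limit of 8.5 g/l is 0.85 g/dl, and read literally it excludes effectively nobody: at most 0.13 expected women in 716 over the assumed range, and under 0.002 where the assumed mean is 100 g/l or more. This contradicts the safety purpose that the Discussion assigns to the exclusions. The conclusion rests on the assumed distribution only for the exact figures, because every combination tried leads to the same place.

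It is probably a unit slip by a factor of ten. No misapplication at any site is shown, the number of women affected is unknown and may be zero, and the sample size and primary analysis are untouched. It deserves correction because it is an eligibility threshold that six sites have to apply, and not background text.

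**What to change.** - Reconcile both the value and the unit of the haemoglobin criterion with the full protocol and the case record form. Do not presume that only the unit is wrong.
- Correct the printed criterion to agree with what that check shows.
- Check that the eligibility form, and any haemoglobin range check in the database, use the same unit as the criterion.
- Leave the cut-off itself to the clinical team. None is proposed here.

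The cost is a short correction to the text and a check of two forms and one database query. Nothing in the design, sample size or analysis has to change.

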### Sample size

The success rate of medical abortion is 95%
[31,32] resulting in a complication rate estimation of 5% in both groups. The primary outcome define the sample size estimation where the 5% non-inferiority margin (delta) establishes the non-inferiority of the home-based self-assessment following medical abortion as compared to the routine clinic follow-up. The delta margin is defined by the clinical assessment standpoint where a 5% difference does not have clinical importance. To proof the non-inferiority of the intervention at a significance level of α = 0,05 and a power of 80%, 596 women are needed. The lost to follow-up estimation of 20%, based on field-testing in the study area, resulted in a final sample size of 716 women. A two-sided 95% confidence interval (CI) (or a one-sided 97,5% CI) will determine the difference in percentage of women requiring surgical intervention from the two groups.

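### The 20% loss allowance was computed as 596 × 1.2, so 716 women do not leave the 298 evaluable per group that the protocol requires

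*Protocol article*

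**What the plan says.** The Sample size section of the protocol article sets the planning values. It assumes a 95% success rate, "resulting in a complication rate estimation of 5% in both groups". The margin is 5 percentage points. The protocol then states that "at a significance level of α = 0,05 and a power of 80%, 596 women are needed", and it bases the comparison on a two-sided 95% interval, equivalently a one-sided 97.5% one. For attrition it adds: "The lost to follow-up estimation of 20%, based on field-testing in the study area, resulted in a final sample size of 716 women".

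The Discussion repeats the 20% loss assumption and ties it to a requirement in each group: "the total study sample required is 716 women, where 298 women with evaluated end point in each group is required to maintain power".

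Allocation is equal: the Randomisation procedure section describes blocks that balance the two groups within each clinic.

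**The concern.** A loss rate found by following enrolled women is a fraction of those enrolled. To end with a required number of evaluable women, that number must be divided by one minus the loss rate. Multiplying it by one plus the loss rate gives too few. The figure 716 looks like the result of multiplying.

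If so, the protocol makes three statements that conflict: 716 randomised, 20% lost, and 298 evaluable per group for 80% power. This is a non-inferiority trial, where an inconclusive result is judged against the planned size and power, so those figures should agree with each other.

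**Working it through.** **Inputs**
- Success rate 95% in both groups, margin 0.05, power 80%, 596 evaluable in total, 20% loss, 716 final: Sample size section.
- One-sided 0.025, from the two-sided 95% interval: Sample size section.
- 298 evaluable per group required: Discussion.
- 1:1 allocation: Randomisation procedure section.

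**Step 1. Reproduce the base size.** With the unpooled normal approximation for the non-inferiority of two proportions:

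n per group = (z₀.₉₇₅ + z₀.₈₀)² × 2p(1 − p) / δ²
= (1.960 + 0.8416)² × 2 × 0.95 × 0.05 / 0.05²
= 298.3

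This agrees with the stated 298 per group, 596 in total. A one-sided 0.05 would give 235 per group, so the protocol's α corresponds to one-sided 0.025, in line with its interval. The base figure is sound.

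**Step 2. Reproduce 716.**
- 596 × 1.2 = 715.2, rounded up to 716.
- By group: 298 × 1.2 = 357.6, rounded up to 358, and 2 × 358 = 716.

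The division form, 596 / 0.80 = 745, does not give 716.

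**Step 3. Apply the stated loss to the stated size.**
- 716 × 0.80 = 572.8 evaluable, about 286 per group.
- Shortfall: 596 − 572.8 = 23.2 in total, about 12 per group.
- Loss that 716 can absorb: 1 − 596/716 = 120/716 = 16.8%.

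**Step 4. Power at that size.**

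SE at 286 per group = √(2 × 0.0475 / 286) = 0.01823
Power = Φ(0.05 / 0.01823 − 1.960) = Φ(0.783) = 0.783

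| Evaluable per group | Normal approximation | Exact binomial, Wald interval |
|---|---|---|
| 298 and 298 | 80.0% | 79.9% |
| 286 and 286 | 78.3% | 78.7% |

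**Step 5. Size that keeps 298 per group at 20% loss.** 298 / 0.80 = 372.5, rounded up to 373 per group, or 746 in total. That is 746 − 716 = 30 more women.

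**Step 6. Unequal loss (illustration).** The protocol gives no loss rates by group. Assume the 20% splits as 10% at home and 30% in the clinic:
- 358 × 0.90 = 322 home and 358 × 0.70 = 251 clinic.
- Power is 77.8% by the normal approximation and 78.8% by the exact method.

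Compared with equal loss, power moves by about half a point or less, and the direction depends on the method. The clinic group would be 298 − 251 = 47 below the per-group requirement, but the conclusion does not rest on this scenario.

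**The case against.** The arithmetic is not open to dispute, but there is a fair case that it matters little.

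**Small effect.** The cost is 1.2 to 1.6 percentage points of power. Margin, α and allocation are untouched. The estimate is not biased, and the false non-inferiority rate does not rise. This stands, and it is why a wording change is enough.

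**Outcome retrieval.** The section on additional procedures and loss to follow-up plans phone or home contact within three months to establish the outcome of women who were lost and have no clinical records. The home-group sections add two further contact attempts and review of clinical records for up to a month. Of the 716 × 0.20 = 143 women lost, recovering about 143 − 120 = 23 would restore 596. So 286 per group is a planning figure rather than a forecast. But the protocol does not say that its 20% excludes women recovered later, so retrieval does not reconcile the stated numbers.

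**Unequal loss.** The Discussion says the travel incentive raised clinic follow-up enough for the study's purpose. It also says clinic follow-up stayed below home follow-up, and it names clinic dropout as a limitation. Without rates by group, the further shortfall in the clinic group cannot be sized, and Step 6 shows little added effect on power.

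**Rounding.** Rounding 298.3 up to 299 would give 299 / 0.80 = 373.75, or 374 per group and 748 in total. The figure 746 is the one that preserves the protocol's own 298.

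**Conclusion.** The concern holds. The base size of 596 is correct, and only the loss adjustment is wrong. With 20% of randomised women lost, 716 leaves about 286 evaluable per group against the stated 298. Power is about 78% (78.3% normal approximation, 78.7% exact) instead of 80%, and the loss that 716 tolerates is 16.8%.

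This rests on the protocol's own planning values, on reading the 20% as a proportion of women randomised, and, for the 286, on equal loss in both groups. The effect on the trial is small, but the statement is wrong in two places and can be shown to be wrong from the protocol alone.

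**What to change.** Correct the Sample size section and the matching sentence in the Discussion so that size, loss and power agree. The simplest change keeps 716 and adds wording such as: *716 randomised women leave the required 596 evaluable (298 per group) if loss to follow-up is at most 16.8%; at 20% loss about 286 per group are evaluable and power is about 78%.* This costs wording only, and the stated power or tolerated loss becomes slightly less favourable.

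If the sponsor prefers to keep 80% power at 20% loss, the target becomes 746 randomised (373 per group), described as the number that preserves the protocol's 298 per group. That costs 30 more women, and the correction does not depend on it.
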